#### 9.4.5 BASELINE DESCRIPTIVE STATISTICS

Descriptive statistics of the cohort will be based on the 6 month observation period. These will include baseline height velocity, height SDS, body proportions, quality of life score, and adverse events. They will be described as noted in Section 9.4.1 above.

#### 9.4.6 PLANNED INTERIM ANALYSES

There are no planned interim analyses. The study will only be discontinued if safety stopping criteria described in **Section 7.1** are met.

#### 9.4.7 SUB-GROUP ANALYSES

Analyses will be stratified by the following subgroups: age, sex, and genetics (presence of a pathogenic or likely pathogenic variant in an individual genetic subgroup).

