**Objectives:**

The primary objectives of the study are as follows:

- To evaluate the safety and tolerability of daily subcutaneous (SC) injections of vosoritide administered for 12 months in patients with selected genetic causes of short stature
- To evaluate the change from baseline in age-sex standardized annualized growth velocity after 12 months of daily SC injections of vosoritide in patients with selected genetic causes of short stature

- To evaluate the change from baseline in age-sex standardized height standard deviation score (SDS) after 12 months of daily SC injections of vosoritide in patients with selected genetic causes of short stature

The secondary objectives of the study are as follows:

- To evaluate changes in body proportions from baseline after 12 months of daily SC injections of vosoritide
- To evaluate changes from baseline in bone age/chronological age after 12 months of daily SC injections of vosoritide

The exploratory objectives of the study are as follows:

- To evaluate the pharmacokinetic (PK) profile of vosoritide in patients with selected genetic causes of short stature
- To evaluate changes from baseline in bone mineral density (BMD) after 12 months of daily SC injections of vosoritide
- To evaluate changes from baseline in vosoritide activity biomarkers and bone/collagen biomarkers after 12 months of daily SC injections of vosoritide
- To evaluate immunogenicity and assess impact on safety and efficacy measures after 12 months of daily SC injections of vosoritide
- To explore the relationship between genetic etiology and safety and efficacy
- To evaluate changes from baseline in quality of life using the QoLISSY scale after 12 months of daily SC injections of vosoritide

During the extension study, all of the primary, secondary and exploratory aims will remain the same, but the timeframe will be extended from 12 months until growth cessation or subject withdrawal from the study.

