**Description of**

**Sites/Facilities Enrolling**

**Participants:**

**Description of Study**

**Intervention:**

This is a single center study at Children's National Hospital. Recruitment will occur throughout the United States, and patients will be brought to Children's National Hospital for all study visits.

This is a pediatric, Phase I/II, open-label single dose study of up to 75 subjects with selected genetic causes of short stature. Subjects who are 3 to 10 years old inclusive for males and 9 years old inclusive for females who have genetic defects in one of the categories defined in the inclusion criteria and meet all eligibility requirements will participate. After enrollment, subjects will be followed for a 6 month observation only period to establish a baseline height velocity as well as safety profile and quality of life assessment. Vosoritide will then be administered daily via subcutaneous injection at a dose of 15  $\mu\text{g}/\text{kg}/\text{day}$  for 12 months. Subjects with a positive response (as defined in the inclusion criteria for extension phase) to therapy will be given the option to continue in the extension phase of the study during which they will continue to receive vosoritide until growth cessation or subject withdrawal from the study.

PK sampling as well as safety monitoring will be conducted for all subjects on the first day that the study drug is received. The safety monitoring includes a minimum of 8 hours post-dose observation on the first day of dosing. Vital signs will be monitored frequently on that day, including approximately every 10-20 minutes for the first 2 hours post dose. Additional assessments include anthropometric measurements, physical examination, laboratory monitoring, ECG, DXA scan, bone age and spine X-rays. On day 2, the subject will return to the clinical research center for their second injection as well as 2 hours of post-injection monitoring. On days 3-5, subjects will receive a daily telephone call to review symptoms and issues with medication administration. After day 5, phone calls will occur on a bi-weekly schedule in-between study visits for months 1-5. During all telephone calls, adverse events as well as medication administration compliance will be assessed.

Subjects will return to Children's National Hospital for visits at 6 and 12 months. At those visits, anthropometric and safety assessments will be obtained as well as additional PK data at the 6 and 12 month visit.

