### 4.2 SCIENTIFIC RATIONALE FOR STUDY DESIGN

In this study, we are focusing on six specific genetic subgroups causing short stature. These six groups all share a common final pathway of growth inhibition via increased activation of ERK1/2 signaling in the chondrocyte (the pathway targeted by vosoritide). These groups are also each relatively rare and within each group there is significant heterogeneity in the severity of short stature. Therefore, we think it is reasonable to combine the six groups into a single study cohort. To control for the interindividual variability, each subject will serve as his or her own control via the baseline 6 month observation only period. We propose to include up to 75 subjects in order to have at least 10 subjects in each subgroup. As the response to vosoritide therapy in this group is unknown, no formal power calculations are

planned. Rather, this is an exploratory study in a rare disease population, and we seek to obtain initial data which will influence future study planning. Additionally, at this time, it is not feasible to recruit a large enough cohort of any of the specific genetic causes to make this a meaningful study. It is difficult to predict the anticipated distribution of patients between each subgroup. In addition to the whole cohort analysis, exploratory analyses will be performed based on underlying genetic etiology. In the future, a randomized controlled study will be required in order to definitively prove efficacy. That is not the goal of the current study as this is a proof of principle study to assess whether subjects meeting these inclusion criteria have the potential to respond to vosoritide therapy.

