### 5 STUDY POPULATION

#### 5.1 INCLUSION CRITERIA

Inclusion and exclusion criteria will be pre-screened based on information provided by the referring clinician. All inclusion and exclusion criteria will then be verified at the screening visit and official screening laboratory studies will be performed as part of that visit. There will be no birth weight or length inclusion or exclusion criteria.

In order to be eligible to participate in this study, an individual must meet all of the following criteria:

1. Parent(s) or guardian(s) are willing and able to provide written, signed informed consent after the nature of the study has been explained and prior to performance of any research-related procedure. Also, subjects under the age of 18 are willing and able to provide assent (if required) after the nature of the study has been explained and prior to performance of any research-related procedure.
2. Stated willingness to comply with all study procedures and availability for the duration of the study
3. Age  $\geq 3$  years 0 days AND  $\leq 10$  years 364 days for males,  $\leq 9$  years 364 days for females
4. Pre-pubertal defined as Tanner Stage 1 breasts in females and testicular volumes  $\leq 3$  cc in males. This must be confirmed at the Day 1 visit prior to initiation of vosoritide.
5. Patient height  $\leq -2.25$  SDS. All height SDS values are calculated using the CDC growth charts/data tables.

6. Patients with pathogenic or likely pathogenic variants in genes known to cause the specific genetic subgroups of short stature listed below are eligible for inclusion in the study. Pathogenicity of variants will be classified as per the American College of Medical Genetics criteria with the exception of *ACAN* mutations as detailed below. Documentation of the presence of the variant must be obtained using a lab results report from a CLIA certified laboratory. Classification of the variant's pathogenicity status will be performed by the Children's National study team.
- A. CNP deficiency due to mutations in *NPPC* – Subjects with heterozygous or homozygous defects in *NPPC* are eligible.
  - B. Hypochondroplasia – Subjects with heterozygous variants in *FGFR3* gene associated with hypochondroplasia are eligible. Subjects with variants in *FGFR3* known to cause achondroplasia or thanatophoric dysplasia or SADDAN syndrome will be excluded.

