### 9.4 STATISTICAL ANALYSES

#### 9.4.1 GENERAL APPROACH

Analyses on all endpoints will be self-controlled, comparing measurements for each subject during follow-up to the same measurements during the baseline period. Thus, all measurements will be summarized for baseline period (control period), and during follow-up (test drug period). Descriptive statistics will be presented for all measures of change from baseline (mean, standard deviation, median, interquartile range, min and max). Comparisons between baseline period and follow-up period will use a paired t-test for continuous endpoints and a chi-square test for dichotomous endpoints. If there are departures from normality or small samples, we will use Mann-Whitney test for comparison of medians and exact Clopper-Pearson test for comparison of dichotomous endpoints.

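### Section 9.4.7 offers only before-after tests within strata for relating genetic etiology to efficacy; with about 10 children per cohort and no between-cohort estimate, equally responding cohorts could often give different verdicts

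*Protocol*

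**What the plan says.** The exploratory objectives (Synopsis and Section 3) include: "To explore the relationship between genetic etiology and safety and efficacy". Section 4.2 states "In this study, we are focusing on six specific genetic subgroups causing short stature" and adds that, besides the whole-cohort analysis, "exploratory analyses will be performed based on underlying genetic etiology".

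On method, Section 9.4.7 states "Analyses will be stratified by the following subgroups: age, sex, and genetics (presence of a pathogenic or likely pathogenic variant in an individual genetic subgroup". Section 9.4.1 makes the analyses of all endpoints self-controlled: "Comparisons between baseline period and follow-up period will use a paired t-test for continuous endpoints". Section 9.4.9, which covers exploratory analyses, deals with pharmacokinetics, bone density, biomarkers, quality of life and antibodies, but not etiology. Section 9.4.7 is therefore the only stated analysis for that objective.

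On size, Section 9.2 aims for approximately 10 children per cohort and stops recruiting cohorts above 15 once 35 children are in. Section 4.2 speaks of at least 10 per subgroup within a total of up to 75. No power, SD or significance level is given. The opening of Section 9 refers further analysis detail to a SAP.

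**The concern.** A relationship between etiology and efficacy is a contrast between cohorts. A before-after test inside one cohort asks whether that cohort changed. Setting six such answers side by side does not say whether the cohorts differ from one another, because in small groups the verdict depends heavily on chance.

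Section 4.2 says the data are meant to shape future studies. If cohorts were ranked by which of them reached significance, or by raw means without an interval for the difference, an etiology that responds as well as the others could look like a weak candidate, and one with a lucky sample could look like a strong one.

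**Working it through.** **Nothing to reproduce.** The protocol states no power or sample-size figure. Six cohorts of 10 make 60, which fits within 75.

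**Inputs.**
- Cohorts: 6 (Section 4.2). Children per cohort: 10 (target, Section 9.2).
- Test: paired t-test (Section 9.4.1), two-sided because the alternative in Section 9.1 is any change. Alpha is not stated; 0.05 is assumed.
- True gain, the same in every cohort: 1.6 or 3 cm/year. These are the response criteria in Sections 5.1 and 8.1, used here only as a scale. They are not design assumptions of the protocol.
- SD of the change in growth velocity: not stated. A range of 1.5 to 3 cm/year is assumed.

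**Step 1: power in one cohort.** The noncentrality is (gain/SD) × √10, with 9 degrees of freedom. For gain 1.6 and SD 2 it is 0.8 × 3.162 = 2.53, and the power p from the noncentral t is 0.616.

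**Step 2: chance of a mixed picture.** With independent cohorts and equal true gains, the chance that some are significant and some not is 1 − p⁶ − (1 − p)⁶. For p = 0.616 this is 1 − 0.055 − 0.003 = 0.942.

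| True gain in all six (cm/year) | SD (cm/year) | Power per cohort | Mixed verdicts |
|---|---|---|---|
| 1.6 | 1.5 | 85% | 62% |
| 1.6 | 2.0 | 62% | 94% |
| 1.6 | 2.5 | 44% | 96% |
| 3 | 1.5 | nearly 100% | 0.1% |
| 3 | 2.0 | 99% | 7% |
| 3 | 2.5 | 92% | 39% |
| 3 | 3.0 | 80% | 73% |

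With no effect in any cohort, p = 0.05 and the chance is 1 − 0.95⁶ − 0.05⁶ = 26.5%.

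Mixed verdicts are more likely than not when gain/SD lies between 0.25 and 1.14, whatever the measurement scale. At 1.6 cm/year that means an SD above about 1.4 (up to about 6.4); at 3 cm/year, above about 2.6. With 15 children per cohort the lower limits rise to about 1.8 and 3.4.

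**Step 3: spread of the means.** Six cohort means with the same true value, each with standard error SD/√10, span 0.80 SD from lowest to highest on average (simulated; 5th to 95th percentile 0.40 to 1.27 SD). That is 1.2, 1.6 and 2.0 cm/year at SD 1.5, 2.0 and 2.5. At least one of the 15 unadjusted pairwise t-tests is significant in 37% of trials.

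**Step 4: a between-cohort test.** One F-test with 5 and 54 degrees of freedom calls equal cohorts different in 5% of trials (simulated 5.1%). For power, take two cohorts at 1.6 and four at 3.0 cm/year, the grouping of the response criteria. The mean is (2 × 1.6 + 4 × 3.0)/6 = 2.53, and the squared deviations sum to 2 × 0.933² + 4 × 0.467² = 2.61. The noncentrality at SD 2 is 10 × 2.61/4 = 6.5, and the power is 43%. It is 70%, 28% and 20% at SD 1.5, 2.5 and 3.

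**Step 5: age and sex.** Boys are eligible to just under 11 years and girls to just under 10. With ages uniform within these limits, the means are 7.0 and 6.5, a gap of 0.5 year. At an assumed slope of 0.1 to 0.5 cm/year per year of age, the sex contrast shifts by 0.05 to 0.25 cm/year, against a standard error of 2 × √(2/37) = 0.46 (SD 2, 37 per sex).

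**The case against.** The strongest reply is that this belongs to the SAP. Section 9 announces one, the etiology analyses are labelled exploratory, Section 4.2 leaves definitive proof to a later randomized study, and nothing in Section 9.4.7 is false. The rationale for the change to about 10 per cohort (amendment history, version 2.8) is to give pilot evidence of efficacy in each cohort, and within-cohort tests serve that purpose. All of this stands. It limits the point to a better choice of method and supports keeping the within-cohort summaries. It does not remove the point: the protocol fixes self-controlled comparisons for all endpoints and ties nothing else to the etiology objective.

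Some stronger readings are tempting, but the documents do not support them:

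- *That cohorts will be declared different by comparing significance, or that strata are formed one factor at a time.* Section 9.4.7 says neither. It excludes neither a joint model nor cross-classification, and it has no rule for dropping or promoting a cohort.
- *That equal cohorts would usually look different.* This depends on an effect and an SD that the protocol does not give. It fails at 3 cm/year for SDs up to about 2.6, and when there is no effect.
- *That sex is seriously confounded with age, given* "Subjects who are 3 to 10 years old inclusive for males and 9 years old inclusive for females". The gap is about half a year, the analyses are self-controlled, and the primary growth endpoints are age-sex standardized. Some mixing remains for measures in raw units, but it is minor.
- *That some ACAN children fall into no genetic stratum, given* "Pathogenicity of variants will be classified as per the American College of Medical Genetics criteria with the exception of" *ACAN.* Section 5.1 item 6 gives ACAN its own classification rule and lists it as category F under the same heading, so the stratum exists.
- *That cohort estimates must be partially pooled.* This is debatable with six cohorts, and the rationale for version 2.7 treats the populations as distinct.

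**Conclusion.** The point holds in limited form, as a moderate one. For the objective of relating etiology to efficacy, the protocol states only before-after tests within strata and no between-cohort estimate. With about 10 children per cohort, those tests are a poor guide to whether cohorts differ: at a common gain of 1.6 cm/year, identical cohorts would more often than not give mixed verdicts once the SD exceeds about 1.4 cm/year. At a common gain of 3 cm/year the problem is small unless the SD exceeds about 2.6. The conclusion about spread does not depend on the size of the gain: at any SD, six equal cohort means of 10 children span about 0.8 SD on average.

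These figures assume equal cohorts of exactly 10, normally distributed changes with a common SD, and a two-sided 5% level. Actual cohort sizes may be unequal, since 10 is a target and Section 4.2 calls the distribution hard to predict.

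**What to change.** Keep the within-cohort summaries. Add to Section 9.4.7 that differences by etiology will be judged by between-cohort estimates with confidence intervals and one overall heterogeneity test. These come from a single model of the change with cohort (the enrolment categories of Section 5.1 item 6, A to F), age at Day 1 and sex, and not from comparing significance across strata.

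The cost is wording only; no visit, sample or treatment changes. The downside is limited power: about 43% at SD 2 for the split between 1.6 and 3.0 cm/year. The text should therefore say that the estimates and intervals lead, and that a non-significant heterogeneity test does not show that the cohorts respond alike.

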#### 9.4.8 TABULATION OF INDIVIDUAL PARTICIPANT DATA

Individual participant data will be listed for each measure and time point.

#### 9.4.9 EXPLORATORY ANALYSES

PK parameters will be summarized using descriptive statistics. Changes in bone density Z-score will be analyzed similar to the primary efficacy analyses. Change in cGMP, serum collagen X markers, and changes in QoLISSY will be compared via t-test at each time point compared to baseline. Rates of total anti-vosoritide antibodies and neutralizing antibodies will be reported.

### 10 SUPPORTING DOCUMENTATION AND OPERATIONAL CONSIDERATIONS

#### 10.1 REGULATORY, ETHICAL, AND STUDY OVERSIGHT CONSIDERATIONS

##### 10.1.1 INFORMED CONSENT PROCESS

##### 10.1.1.1 CONSENT/ASSENT AND OTHER INFORMATIONAL DOCUMENTS PROVIDED TO PARTICIPANTS

Consent forms describing in detail the study intervention, study procedures, and risks are given to the participant and written documentation of informed consent is required prior to any study assessments. The following consent materials are submitted with this protocol:

- Consent form for subject to be completed by guardian
- Upon approval of the initial English consent forms, the consent forms will be translated into Spanish using a hospital approved translation service. These will be added to the protocol in an administrative amendment. If subjects are recruited who require consents in a language other than English or Spanish, the consent forms will be translated into the appropriate language and approved by the IRB prior to proceeding with enrollment.
- Consent addendum for the extension phase for the subject to be completed by the guardian
- Assent form for subjects in the extension phase to be completed by the subject at the first in-person visit after their 12th birthday

##### 10.1.1.2 CONSENT PROCEDURES AND DOCUMENTATION

The study team will receive referrals for potential participants from pediatric endocrinologists and geneticists throughout the United States. We will request a HIPPA waiver from the IRB for screening these referrals for the purposes of subject recruitment.

Consent forms will be Institutional Review Board (IRB)-approved. The participant/legally authorized representative (LAR) will be given a copy of the consent forms to read and review the document in advance of the Screening Visit. A telephone call will be scheduled to review the details of the study and consent in advance of the screening visit. This is a purely informational call and will not replace the in person consent. Subjects who remain interested in participating will then be scheduled for a Screening Visit.

At the Screening Visit, the principal investigator or a qualified physician co-investigator will explain the research study to the participant and answer any questions that may arise. This conversation will take place in a private room. Verbal assent will be conducted for children age 7 and older. Written assent will not be obtained as all subjects are under age 12 years. A verbal explanation will be provided in terms suited to the participant's comprehension of the purposes, procedures, and potential risks of the study and of their rights as research participants. Participants/families/LAR will have the opportunity to carefully review the written consent form and ask questions prior to signing. The participants/family/LAR should have the opportunity to discuss the study with their family or surrogates, or think about it prior to agreeing to participate. The participant will sign the informed consent document prior to any procedures being done specifically for the study. Participants/families/LAR must be informed that participation is voluntary and that they may withdraw from the study at any time, without prejudice. A copy of the informed consent document will be given to the participants/families/LAR for their records. The informed consent discussion will be documented in the research record.

For subjects with a good response to therapy at the 12 Month Visit, they will be given the opportunity to continue into the extension phase of the study. If they choose to continue in the extension phase, they will sign a consent addendum. The same procedures will be used as above. Any subjects who have reached age 12 years will be asked to sign a written assent form at the time of enrollment in the extension phase. If they become 12 years old while in the extension phase, they will be asked to sign the written assent form at their next in-person visit. Subjects who do not assent to continue in the study will be withdrawn from the study.

For subjects who do not speak English, we will follow the same procedures but will use a certified interpreter for all interactions. A consent form in the subject's primary language will be used to document consent after verbally reviewing with the interpreter the entire informed consent document.

---

#### 10.1.2 STUDY DISCONTINUATION AND CLOSURE

This study may be temporarily suspended or prematurely terminated if there is sufficient reasonable cause. Written notification, documenting the reason for study suspension or termination, will be provided by the PI to study participants, BioMarin, and regulatory authorities. If the study is prematurely terminated or suspended, the Principal Investigator (PI) will promptly inform study participants, the Institutional Review Board (IRB), and BioMarin and will provide the reason(s) for the termination or suspension. Study participants will be contacted, as applicable, and be informed of changes to study visit schedule.

Circumstances that may warrant termination or suspension include, but are not limited to:

- Determination of unexpected, significant, or unacceptable risk to participants
- Insufficient compliance to protocol requirements

- Data that are not sufficiently complete and/or evaluable
- Loss of funding and/or support from BioMarin

Study may resume once concerns about safety, protocol compliance, and data quality are addressed, and satisfy the IRB, DSMB, BioMarin and/or Food and Drug Administration (FDA) as necessary.

---

